**Bland-Altman analysis for repeated measurements**

After all data are classified into the two groups based on the PI ≤1 and PI >1, Bland-Altman analysis will be performed in each group to calculate the bias, precision, and the 95% limits of agreement.

**11.3.2 Analysis of the secondary outcome**

(1) The bias between the two devices is calculated by the linear mixed-effects regression model for the primary outcome.

(2), (3) For the evaluation of the interchangeability, the percentage error and interclass correlation coefficients with 95% confidence interval between the two devices are calculated.

(4) Linear mixed-effects regression model

The dependent values: The mean difference of CO, SV, and SVV between the two devices

The independent value: PI value

The random effect: Subject

The CO, SV, and SVV data pairs of the two devices are divided into two groups based on PI value 1. Bland-Altman analysis for repeated measurements will be performed in each group, and bias, precision, and 95% limits of agreement are calculated.

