**9.3. Measuring schedule**

One measurement period is defined as 15 minutes. In the operating room, anesthesiologists who are not involved in the data analysis plan for a two-hour operation that will result in at least 8 measurement periods from skin incision until skin suture when the hemodynamic condition is relatively stable. One hundred twenty data pairs will be obtained from one subject in the operating room. In the ICU, at least 2 measurement periods are planned per subject until 4 hours after arrival in the ICU, so that the total number of measurement periods per subject will be at least 10. We plan on obtaining 150 data points per subject, at least. However, these are just target numbers. It is possible to increase or decrease the measurement periods depending on the actual operation situation or the time of admission to the ICU.

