**10.2 Secondary endpoint**

(1) The beta coefficient of the bias using the linear mixed-effects model between arterial pressures measured with the ClearSight versus those measured with an arterial catheter.

(2) The percentage error of the arterial pressure.

(3) Interclass correlation coefficients of the arterial pressure.

(4) The beta coefficient of the CO, SV, and SVV calculated by the linear mixed-effects regression model.

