**11.3. Methods and items**

**11.3.1** **Analysis of the primary outcome**

**Linear mixed-effects regression model**

**(calculating the SD of the bias between the two devices)**

Response variable: The mean differences between the two devices.

Covariate: Binarized PI (PI ≤1 and PI >1), heart rate, body temperature, and the mean values of the APcs and the IAP.

Random effect: Subject

The model allows the variances of the bias to differ depending on the binarized PI.

Based on the results of this model, the ratio of the adjusted SD of bias is calculated.

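### The model for the PI effect on mean bias has no patient-specific PI shift, so the standard error of that beta is too small if the shift differs between patients; the effect on the primary SD ratio is minor.

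*Protocol*

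**What the plan says.** Section 11.3.1 of the protocol (summarised in 0.5) sets out one mixed model for the difference between the devices.

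- Fixed part: "Covariate: Binarized PI (PI ≤1 and PI >1), heart rate, body temperature, and the mean values of the APcs and the IAP".
- Random part, in full: "Random effect: Subject".
- Residual part: "The model allows the variances of the bias to differ depending on the binarized PI".
- Primary result: "Based on the results of this model, the ratio of the adjusted SD of bias is calculated".

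Section 10.2 opens its list with the comparison against the catheter: "The beta coefficient of the bias using the linear mixed-effects model between arterial pressures measured with the ClearSight". Section 11.3.2(1) takes it from the same fit: "The bias between the two devices is calculated by the linear mixed-effects regression model for the primary outcome". PI is averaged each minute (7.1, data acquisition), and on volume section 9.3 says "We plan on obtaining 150 data points per subject, at least".

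**The concern.** PI is a within-patient condition: one patient can supply minutes in both PI states. A random intercept lets patients differ in their overall bias but not in how far the bias moves when PI falls to 1 or below. The protocol itself gives reason to doubt a common shift. Section 1 names several possible causes of poor finger perfusion (high vascular resistance, vasopressors, edema), and section 7.1 records edema, hypertension history and vasopressor dose, none of which enters the model.

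If the shift does vary, the beta is replicated over about 25 patients, while the model computes its standard error as if it were replicated over thousands of rows. The average effect of PI on bias would then be reported with more precision than the data hold. A lesser consequence is that the unmodelled shift passes into the residuals, mainly of the rarer PI state, and those residuals feed the primary SD ratio.

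**Working it through.** **Inputs from the protocol.** 25 evaluable patients, SD ratio 1.35, alpha 0.05, power 0.90, 10 measurement periods per patient, equal numbers of points in the two PI states, and 8.4 mm Hg (all 11.1); at least 150 rows per patient (9.3).

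**Assumptions.** Section 11.1 calls 8.4 mm Hg the bias; here it serves as the residual SD. Rows within a patient are independent. The true mean PI shift is 0. The between-patient SD of the shift, tau, is not in the protocol and is varied from 0 to 6 mm Hg. Heart rate, temperature and mean pressure are left out.

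**The plan's own figure.** A two-sided F-test for an SD ratio of 1.35 at alpha 0.05 and power 0.90 needs 119 readings per PI group, 238 in all. At 10 per patient that is 24 patients, against the stated 25. The planned number is reproduced to within one patient, and it rests on 10 readings per patient, not 150.

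**Standard error of the beta, 50:50 mix.** Rows: 25 × 150 = 3,750.

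- Model SE = 2 × 8.4 / √3750 = 0.274.
- True SE = √(0.274² + tau²/25).
- Error of a nominal 5% two-sided test = 2 × [1 − Φ(1.96 × model SE / true SE)].

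| tau (mm Hg) | True SE | Error, closed form | Error, REML simulation |
|---|---|---|---|
| 0 | 0.274 | 5% | 4-6% |
| 1 | 0.340 | 11% | not run |
| 2 | 0.485 | 27% | 21-25% |
| 4 | 0.846 | 52% | 43-47% |

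The simulation column covers settings with equal SDs in the two PI states. At 50:50 and tau 4 the simulated model SE was 0.28 against an empirical SD of 0.79.

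**Same check with 10 rows per patient.** Model SE = 2 × 8.4 / √250 = 1.063. At tau 4 the true SE is √(1.063² + 16/25) = 1.330 and the error about 12%; simulation gave 7-11%. The inflation is modest.

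**Leak into the primary ratio.** Let p be the share of minutes at PI ≤1. The patient intercept absorbs roughly p times that patient's shift. This leaves extra residual variance of tau²(1−p)² in low PI and tau²p² in high PI. With a true ratio of 1.00, the fitted ratio is about √[(8.4² + tau²(1−p)²) / (8.4² + tau²p²)].

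| p | tau 2 | tau 4 | tau 6 |
|---|---|---|---|
| 0.2 | 1.02 | 1.07 | 1.14 |
| 0.5 | 1.00 | 1.00 | 1.00 |
| 0.8 | 0.98 | 0.94 | 0.88 |

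Simulation at p = 0.2 gave 1.07 (tau 4) and 1.16 (tau 6) with the same low-PI share in every patient, and 1.03 and 1.08 when the share varied. With so many rows treated as independent, an equal-SD test in those four settings still rejected 20-96% of the time.

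**Check of the remedy.** With a random PI slope (150 runs per setting, tau 2 to 6), the error of the beta was 3-5% using t with 24 degrees of freedom, apart from one setting at 9%. Model SE and empirical SD agreed (0.88 and 0.88 at 50:50, tau 4), and the SD ratio returned to 0.997-1.001.

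**The case against.** **The protocol does not spell out a random intercept.** Naming subject can be read as naming the grouping factor, with the covariance structure left to an analysis plan. That is possible, but subject is the only random term listed, and the ordinary reading is an intercept. The ambiguity is itself worth removing.

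**No test of the beta is planned.** This stands. Sections 10.2 and 11.3.2(1) ask for a coefficient and set no significance rule. A reader might infer that secondary endpoint 1 would often be falsely declared significant; the documents do not support that as a prediction. What remains is that any standard error, interval or test reported from the fit would be too optimistic.

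**The size is assumed.** This also stands. Nothing in the protocol shows that the shift varies, and the large figures need 150 independent rows per patient. Sections 7.1 and 9.3 support one-minute rows, but not their independence.

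**The primary endpoint.** A reader might infer that the primary ratio is seriously distorted. It is not at the planned 50:50 mix with a true ratio of 1, and the movement is a few percent up to tau 4. The large movements need tau 6 and a lopsided mix together. The mix is also not the only driver: with a true ratio of 1.35 at 50:50 there is slight upward drift, to 1.36-1.39 at tau 4-6.

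**A random slope changes what the primary ratio measures.** A clinician seeing a low PI does not know that patient's own shift, so it is arguably part of the disagreement. This is a fair reason not to replace the planned ratio.

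**CO, SV and SVV.** Extending the point to section 11.3.2(4) is tempting, but that model enters PI value, not stated as binarized, and nothing was computed for it.

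**Conclusion.** The point holds conditionally and concerns mainly secondary endpoint 1. With a subject intercept alone and at least 150 rows per patient, even a small between-patient shift SD of 1 to 2 mm Hg, against a residual SD of 8.4, raises the error of a nominal 5% test to about 11% and 21-27%. It is about 5% if all patients share one shift. The figures rest on an assumed shift SD, independent rows and 8.4 mm Hg taken as an SD.

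For the primary SD ratio this is a caveat, not a finding of bias: the rarer PI state gets a somewhat inflated SD if the mix departs from 50:50, and nothing in the design enforces that mix. The documents do not support an unconditional statement that the analysis is strongly anticonservative. The model should be amended for the beta and checked for the ratio.

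**What to change.** - **PI beta, section 11.3.2(1):** add a subject-level random slope for binarized PI to the random intercept, and keep the PI-specific residual variance. Use small-sample degrees of freedom for the interval, and report the estimated between-patient SD of the shift.
- **Primary SD ratio, section 11.3.1:** keep the planned ratio and report the random-slope version beside it as a sensitivity analysis. State in advance whether a patient's own PI shift counts as part of the SD of bias.

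The cost is one model term and no new data. The interval for the beta will be wider. The fit may fail to converge, in which case drop the intercept-slope correlation. The change does not deal with serial correlation between minutes, which needs separate treatment.

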**1. Object and meaning**

ClearSight™ (Edwards Lifesciences Corporation, Irvine, CA USA) is a noninvasive monitor for measuring the arterial blood pressure, cardiac output (CO), or the other hemodynamic parameters such as stroke volume index (SVI), stroke volume variation (SVV), or systemic vascular resistance index (SVRI). With widespread use of the ClearSight, healthcare providers will be able to provide care in a less invasive manner.

The agreement between the arterial pressure values measured by the ClearSight (APcs) and the arterial catheter-based blood pressures (IAP) has been examined by several studies.[1-4] In patients undergoing cardiac surgery or those in the intensive care unit (ICU) after cardiac surgery, the APcs shows sufficiently good bias and precision to substitute for IAP. However, APcs is not reliable in critically ill patients or in those receiving vasopressors to maintain their blood pressure.[5-7] It has been speculated that the unreliability may be due to reduced finger perfusion from high peripheral vascular resistance, continuous vasopressor administration, and/or edema, but the evidence is lacking.

We hypothesized that lower peripheral perfusion would affect the agreement between the arterial APcs and the IAP. As an indicator of peripheral perfusion, we chose the perfusion index (PI) measured by pulse oximetry, which is calculated as the ratio of the pulsatile infrared signal to the non-pulsatile infrared signal in the peripheral tissue.[8] The PI can be obtained continuously and noninvasively, and lower values indicate peripheral hypoperfusion or vasoconstriction.

The primary objective of this study is to assess whether the PI affects the agreement between APcs and IAP. The secondary objective of this study is to assess whether the PI affects the agreement between cardiac output, SVI, SVV, or SVRI as measured by the ClearSight and those measured by the FloTrac system (Edwards Lifesciences Corporation, Irvine, CA USA). If the PI value is determined to be an indicator of the agreement of the ClearSight and the invasive arterial pressure, it may be possible to judge the reliability of the APcs value in real time. Our study may beneficially contribute to patients by providing a minimally invasive solution.

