**10. Definition of the endpoints**

**10.1 Primary endpoint**

The standard deviation (SD) of the bias between arterial pressures measured with the ClearSight versus those measured with an arterial catheter.

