**11. Statistical analysis**

**11.1 Sample size**

**Estimated sample size before starting the recruitment: 30 cases**

**Grounds:** First, the cut-off value of the PI is defined as 1 (described in the pulse oximeter manual as a measure of hypoperfusion and clinical acceptability). Second, it is assumed that the acquirable number of data points of the PI ≤ 1 and those points of the PI > 1 are equal. The bias of the arterial blood pressures between the two devices is assumed to be 8.4 mm Hg based on a past study.[9] The total number of data points is determined to detect a 1.35-fold difference in the ratio of the SD of the bias between those with a PI ≤1 and >1. Assuming that at least 10 measurement periods can be secured per subject, the sample size is calculated by an *F*-test to be 25 with an *α* error of 0.05 and a 1–*β* of 0.9. We are planning for a sample size of 30 cases in anticipation of possible dropout. According to the Association for the Advancement of Medical Instrumentation (AAMI) SP10.2002, a minimum of 15 subjects and 10 readings per subject should be reported for the proof of accuracy for noninvasive blood pressure (NIBP) devices. This criterion has been applied in the past in similar studies about the accuracy of the noninvasive arterial pressure monitor.[10] In comparison to the above, our sample size is considered to be roughly reasonable. The measurement period should be set as evenly as possible during the operation.

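### For CO, SV and SVV the planned model estimates only a shift in the mean device difference; the effect of PI on spread, the protocol's own criterion of agreement for pressure, is described but never compared

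*Protocol*

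**What the plan says.** Section 1 frames the question as one of agreement: "The secondary objective of this study is to assess whether the PI affects the agreement between cardiac output, SVI, SVV, or SVRI", ClearSight against FloTrac.

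For arterial pressure the protocol measures agreement by spread:
- The primary endpoint (10.1) is "The standard deviation (SD) of the bias between arterial pressures measured with the ClearSight versus those measured with an arterial catheter".
- The sample size (11.1) rests on the same quantity: "The total number of data points is determined to detect a 1.35-fold difference in the ratio of the SD of the bias" between low and high PI.
- The primary model (11.3.1) is built to deliver it: "The model allows the variances of the bias to differ depending on the binarized PI". The ratio of adjusted SDs is then calculated.

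For the flow parameters the endpoint (10.2, item 4) is "The beta coefficient of the CO, SV, and SVV calculated by the linear mixed-effects regression model". The model in 11.3.2(4) is set out separately. Its response is "The dependent values: The mean difference of CO, SV, and SVV between the two devices", its predictor is given as "The independent value: PI value", and subject is the random effect. It has no line on variance.

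The same item splits the data pairs at a PI of 1 and adds: "Bland-Altman analysis for repeated measurements will be performed in each group, and bias, precision, and 95% limits of agreement are calculated".

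**The concern.** Agreement has two parts, the mean difference and its scatter. For pressure the protocol estimates both from one model: the SD ratio as primary endpoint and beta as secondary endpoint 10.2(1). For CO, SV and SVV only beta remains as an endpoint, and its model has no stated term through which PI could act on scatter.

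The effect the trial was designed to find for pressure is a wider scatter at low PI. If PI acts on the flow parameters in the same way, without moving the mean, the only inferential analysis named for them will show nothing. A null beta could then be reported as no effect of PI on agreement, while the Bland-Altman limits differ between groups with nothing to say whether that difference exceeds chance.

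**Working it through.** **1. The plan's own figure.** The protocol gives no calculation for CO, SV or SVV. Its one calculation is for the SD ratio in pressure (11.1): ratio 1.35, alpha 0.05, power 0.9, equal numbers of points with PI ≤1 and >1, and 10 measurement periods per subject, giving 25 subjects. A two-sided F-test on two variances, with points treated as independent, needs 119 points per group. That is 2 × 119 = 238 points, and 238/10 = 23.8, so 24 subjects. At 25 subjects (125 points per group) power is 0.914. The stated figure is reproduced to within one subject, which confirms that the design was sized on a comparison of spread.

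**2. What beta can detect.** Write the device difference for reading j in subject i as

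d_ij = β0 + β·L_ij + u_i + e_ij,

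where L = 1 if PI ≤1, u_i is the subject effect, and e_ij has SD σ when PI >1 and rσ when PI ≤1. If PI acts on spread alone, β = 0 for every r. A test of β then rejects only at its false positive rate, whether r is 1.35, 2 or larger. The same holds if PI enters as a continuous value. This step needs no assumption about the data.

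**3. What else covers spread.** The analyses of agreement in the protocol compare as follows.

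| | Pressure | CO, SV, SVV |
|---|---|---|
| Mean shift by PI | beta, 10.2(1) | beta, 10.2(4) |
| Spread within each PI group | Bland-Altman, 11.3.1 | Bland-Altman, 11.3.2(4) |
| Spread compared between PI groups | SD ratio from model, 11.3.1 | none |

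**4. Secondary remark: the standard error of beta.** Suppose PI is binarized, the model has one common variance, and a share p of readings has PI ≤1. Ignoring clustering,

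model variance ∝ [p·r² + (1 − p)]·[1/p + 1/(1 − p)]

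true variance ∝ r²/p + 1/(1 − p)

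R = √(model/true), and type I error = 2·[1 − Φ(1.96·R)].

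Take r = 1.35, so r² = 1.8225. The protocol states this ratio for pressure only; using it here is an assumption. The shares 0.2 and 0.8 are also assumptions; 0.5 is the protocol's.

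- p = 0.2: model 1.1645 × 6.25 = 7.278; true 9.1125 + 1.25 = 10.3625; R = 0.838; type I error 0.10.
- p = 0.5: model 1.41125 × 4 = 5.645; true 3.645 + 2 = 5.645; R = 1.000; type I error 0.05.
- p = 0.8: model 1.658 × 6.25 = 10.3625; true 2.278 + 5 = 7.278; R = 1.193; type I error 0.02.

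Simulation of a random-intercept REML fit (25 subjects × 10 points, 1,500 runs per setting) gave type I errors of 0.107, 0.052 and 0.027. With PI as a continuous predictor and the change in spread still placed at PI 1, it gave 0.045, 0.039 and 0.023. Simulation error near 0.05 is about √(0.05 × 0.95/1500) = 0.006. The simulations assume a between-subject SD of 0.7 times the residual SD at PI >1, subject shares of low PI drawn from a beta distribution (binarized case), lognormal PI (continuous case), and no autocorrelation. None of these is in the protocol.

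**The case against.** The best defence is that item (4) does not stop at beta. The Bland-Altman analysis in each PI group reports precision and limits of agreement, so a doubled spread would be visible on the page. That stands. A reader might infer that the plan cannot answer whether PI affects agreement in the flow parameters. That is true of the model alone, not of the plan. What is missing is a comparison between groups with an interval.

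A reader might also infer that the standard error of beta is wrong under the trial's own hypothesis, so that false positives follow. The documents do not support this:
- At the equal split assumed in 11.1, the common-variance standard error is right.
- Away from that split the error can go either way. Section 2.1 expects this population to yield low PI values more often, and a high share of low PI makes the test conservative.
- If PI is continuous, the simulated settings show no inflation.
- The hypothesis in Section 1 and the ratio of 1.35 both concern pressure.

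Two more points are fair. A mean-shift beta is a legitimate part of agreement. And a common variance is inferred from the absence of the line that 11.3.1 contains; 11.3.2(4) neither states nor excludes it. Likewise, the bare reference to the PI value may be loose wording, since Section 0.5 says all data are split at 1. A statistical analysis plan could settle both details. It would not by itself change the endpoint, which 10.2(4) fixes as a beta coefficient.

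**Conclusion.** The point holds in limited form. The secondary objective is agreement, yet the only inferential result named for CO, SV and SVV is a mean shift, while spread is described by PI group and never compared. That a pure widening of spread leaves beta at zero follows from the model and rests on no assumption.

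The standard-error remark is conditional on binarized PI, one common variance, an SD ratio of 1.35 borrowed from pressure, and a PI split other than equal. Within those assumptions type I error runs from about 0.10 (20% low PI) through 0.05 (50%) to 0.02-0.03 (80%). With continuous PI the simulations gave 0.02 to 0.045. It supports the fix but is not the reason for it.

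The primary endpoint and the sample size are untouched. The change is worth making but is not critical.

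**What to change.** In 11.3.2(4), use the structure of 11.3.1 for CO, SV and SVV: binarized PI, subject random effect, and residual variance allowed to differ by PI. State the coding of PI explicitly. In 10.2(4), add the SD ratio (PI ≤1 versus >1) with its confidence interval beside the beta coefficient. Keep the Bland-Altman analyses as the descriptive companion.

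This gives spread in the flow parameters an estimate and an interval, and removes the dependence of beta's standard error on the PI split. It needs no new data, and the model is already required for the primary endpoint. The statistical cost is one more variance parameter per outcome. The administrative cost is an amendment: Section 18 lists changes to endpoints as major, needing ethics approval, but lists changes unrelated to the primary endpoint as minor, so the addition has to be classified.

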**11.4 Interim analysis**

Not applicable

**12. Case report forms**

Case report data are reported on the form that includes the patient characteristic data, perioperative data, and case registration. The co-researcher will submit this form to the lead principal investigator after completing the form.

